### Assignment of interventions: blinding

#### Who will be blinded {17a}

Due to the nature of the intervention, participants and yoga teachers will not be blinded to the group allocation. Outcome measures are primarily self-reported. Members of the research team collecting the outcome data over the telephone will take reasonable steps to ensure that they are blind to the participant’s group allocation.

Although GPs will be informed about study participation, they will not be informed about allocation status, reducing the risk of inducing GP behaviour change based on this knowledge. The wider health and social care team will not be informed about study participation or allocation status.

#### Procedure for unblinding if needed {17b}

This is primarily an open trial, so there are no specific emergency unblinding procedures. Group allocation may, if necessary, be revealed to a participant’s GP in response to a yoga-related adverse event.

### Data collection and management

#### Plans for assessment and collection of outcomes {18a}

Data will be collected via participant-completed questionnaires at baseline and at 3, 6, and 12 months after randomisation. Completed outcome data are returned primarily by post but also via telephone where necessary (e.g. for participants who require assistance to complete their questionnaires). Demographic and medical history information will be collected at baseline. All participants will be given a diary to prospectively record their health service use to aid them with completing the health service use section in follow-up questionnaires.

#### Plans to promote participant retention and complete follow-up {18b}

The following plans will be implemented to promote participant retention and complete follow-up:
Yoga teachers will encourage regular class attendance and contact participants who miss two consecutive classes without prior notification.Participants who withdraw from the yoga programme may choose to remain in the trial to provide follow-up data.Participants will receive a £5 shopping voucher or £5 cash with every follow-up questionnaire as a thank you for their continuing participation in the trial.A text message will be sent to participants who have consented to receive this form of communication 1–7 days before each questionnaire is sent, saying that they will shortly receive a questionnaire and to complete and return it as soon as possible. The text message also acts as a prompt for the participant to inform the research team if they have moved address.A reminder letter will be sent if the questionnaire has not been returned within 14–21 days.A researcher will call the participant to complete the questionnaire over the phone if it has not been returned within 28 days.If a questionnaire is returned incomplete or with errors, a researcher will call the participant for clarification or completion of missing or invalid data.Participants will be advised that they are able to phone a member of the research team if they require assistance with completing a questionnaire.A newsletter containing information about trial progress and any relevant updates will be sent out to participants via post or email every 3–6 months.After completing the final follow-up questionnaire (12 months), all control participants will receive details of GYY or other suitable yoga classes that they could join on a self-pay basis.After randomisation to the main trial, participants allocated to the control group will be randomised again to receive the offer of a one-off group yoga class, which will take place when the final follow-up is completed, or no offer.

#### Data management {19}

Case report forms will be used to record all the information required from the protocol. Essential trial documentation which individually and collectively permits evaluation of the conduct of the trial and the quality of the data produced will be kept within the Trial Master File. The sponsor will ensure that this documentation is retained for a minimum of 5 years after the conclusion of the trial and a minimum of 20 years in electronic format in accordance with the guidelines on Good Research Practice. Paper data will then be disposed of securely and electronic data will be anonymous of identifiable information.

All study-related information will be stored securely in the coordinating centre at the University of York or at an alternative secure off-site facility. All electronic records will be stored on a password-protected server. All participant data will be identified by a coded identification number to maintain participant confidentiality.

All participant information will be stored in locked cabinets in areas with restricted access. Process evaluation data (e.g. interview audio recordings) will be stored securely on a password-protected server at Northumbria University. Participant data may only be reviewed by authorised persons on the research team or other authorised people to verify that the study is being carried out correctly; all of whom will have a duty of confidentiality. Trial participants will give permission for this authorised review of their data at the time of consent. All names and other identifying information will be removed before the data is analysed and the results presented at conferences and in scientific journals.

#### Confidentiality {27}

Data will be handled in accordance with the Data Protection Act 2018, GDPR legislation, the latest Directive on Good Clinical Practice, and local policy.

#### Plans for collection, laboratory evaluation, and storage of biological specimens for genetic or molecular analysis in this trial/future use {33}

No biological specimens will be collected.

### Statistical methods

#### Statistical methods for primary and secondary outcomes {20a}

Statistical analyses will be described in detail in a statistical analysis plan (SAP) that will be agreed upon with the Trial Steering Committee before all data has been collected. Any subsequent amendments will be clearly stated and justified. The trial will be reported in accordance with the Consolidated Standards of Reporting Trials (CONSORT) guidelines for clinical trials [36]. Baseline data will be summarised using descriptive statistics with no formal statistical comparisons of the baseline data undertaken. All analyses will be conducted on an intention-to-treat basis and using two-sided significance tests at the 5% significance level, unless otherwise stated.

The primary outcome will be analysed using a linear mixed model, including all available follow-up time points. The model will adjust for EQ-5D-5L at baseline and include as fixed effects: time point, trial arm, arm by time interaction, and other covariates specified in the SAP. Patient (to account for the repeated measures) and site will be included as random effects. The overall difference between the two groups over the 12 months from randomisation will be the primary endpoint, but differences at each time point will be extracted for secondary investigations aimed at determining the potential pattern of change. Adjusted mean differences will be presented with an associated 95% CI and *p* value. Different covariance patterns for the repeated measurements will be explored, and the most appropriate pattern will be used for the final model. Model assumptions will be checked, and if they are in doubt, transformations of the outcome data will be considered. Analyses to account for possible clustering by yoga class will also be undertaken by including the class as a random effect, nested within the treatment arm. We shall explore the impact of differing modes of delivery (face-to-face, or online) within subgroup analyses.

The anxiety, depression, loneliness, and PROMIS-29 data will be analysed in the same way as described for the primary outcome. The number of falls experienced by participants over the 12 months will be analysed using a negative binomial regression model. The number and type of serious and non-serious adverse events will be summarised descriptively by randomised group.

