### Sample size {14}

Walters and Brazier [34] in a review paper of the EQ-5D-3L found a difference of 0.074 (mean) or 0.081 (median) to be a minimum clinically important difference among a variety of patients, whilst McClure and colleagues found a difference of 0.063 (mean) or 0.064 (median) for the EQ-5D-5L using simulated data [35]. To be conservative, we took the lowest estimate (0.06) with an estimated standard deviation of 0.20 [21]. Accounting for loss to follow-up of 20%, we need to recruit and randomise 586 participants for the study to have 90% power with 5% significance (two-sided).

Although this is an individually randomised trial, there is a possibility of potential clustering within the intervention arm by yoga class. If we assume an intraclass correlation coefficient of 0.04 and an average class size of 12 in the intervention arm, then with the proposed sample size, we would still retain 84% power to detect the same magnitude of effect (ceteris paribus). In this calculation, we considered the level of clustering at the yoga class level, rather than at the level of the yoga teacher, since we believe this will be the most influential level of clustering. Accounting for potential clustering within the intervention arm only leads to small reductions in power, which could potentially be recovered in the analysis of the repeated measures which is not currently accounted for in the sample size calculation.

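### The primary model leaves out yoga class, so its standard error is too small whenever outcomes vary between classes

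*Protocol article*

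**What the plan says.** The section on statistical methods for primary and secondary outcomes {20a} sets out a linear mixed model over all follow-up visits, with baseline EQ-5D-5L, time, arm and arm by time as fixed effects. On the random part it states: "Patient (to account for the repeated measures) and site will be included as random effects". The primary endpoint is the overall arm difference over 12 months, tested "using two-sided significance tests at the 5% significance level, unless otherwise stated". Class comes later in the same paragraph: "Analyses to account for possible clustering by yoga class will also be undertaken by including the class as a random effect", nested within arm.

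The sample size section {14} does reckon with class. For the basic calculation, "we took the lowest estimate (0.06) with an estimated standard deviation of 0.20". Then: "Accounting for loss to follow-up of 20%, we need to recruit and randomise 586 participants", for 90% power. It continues: "If we assume an intraclass correlation coefficient of 0.04 and an average class size of 12 in the intervention arm", then with the planned number "we would still retain 84% power to detect the same magnitude of effect". It adds that any gain from the repeated measures has not been counted.

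Elsewhere the article plans about 24 courses taught by about 12 teachers, with 12 participants per online course and up to 15 per face-to-face course, all from the intervention arm. Randomisation is stratified by site.

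**The concern.** Participants in one course share a teacher, a group and the social time after class, so their outcomes may be correlated. Controls have no such grouping. The plan lowers its power figure for this correlation, but the model that yields the primary estimate, interval and p value sets it to zero.

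The site term is not a substitute. Each site contributes participants to both arms, so a site intercept largely cancels from the arm comparison. A class effect present in only one arm stays in that comparison as unmodelled variance.

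The main conclusion of the trial is at stake. If the ICC is near 0.04 and the single-time-point calculation applies, a primary p value between about 0.03 and 0.05 would be declared significant without meeting the 5% level.

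**Working it through.** **Inputs from the protocol article.** Difference 0.06, SD 0.20, two-sided 5%, power 90%, loss 20%, 586 randomised, ICC 0.04, 12 per class, about 24 classes, 1:1 overall allocation.

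**Reproducing the plan's figures.**
- n per arm = 2(1.96 + 1.2816)² / (0.06/0.20)² = 233.5, so 234. Allowing for loss, 234/0.8 = 292.5, so 293 per arm and 586 in total. This agrees.
- Design effect in the intervention arm: 1 + (12 − 1) × 0.04 = 1.44.
- Analysed per arm: 586 × 0.8 / 2 = 234.4. SE = 0.20 × √(1/234.4 + 1.44/234.4) = 0.0204. Power = Φ(0.06/0.0204 − 1.96) = 83.7%. This is the stated 84%.

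**Error of the test without class, single time point.** The true SE is √((1 + DE)/2) times the SE that ignores class. The actual two-sided error is 2(1 − Φ(1.96/ratio)).

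| ICC | Analysed per class | DE | SE ratio | Actual error |
|---|---|---|---|---|
| 0.04 | 12 | 1.44 | 1.105 | 7.6% |
| 0.04 | 9.6 (12 less 20%) | 1.344 | 1.083 | 7.0% |
| 0.04 | 15 | 1.56 | 1.131 | 8.3% |
| 0.02 | 12 | 1.22 | 1.054 | 6.3% |
| 0.01 | 12 | 1.11 | 1.027 | 5.6% |

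For 12 per class, the nominal p value that corresponds to a true 5% level is 2(1 − Φ(1.96 × 1.105)) = 0.030. For 9.6 per class it is 0.034.

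**Does the site effect help?** A model with a site random intercept and no class term was simulated at class ICC 0.04, with 3,000 runs per scenario. The layouts were 24 sites with one class or 12 sites with two, 10 or 12 per class, and a site ICC of 0 or 0.02 (the layouts and site ICCs are assumptions). It rejected in 6.9–8.4% of runs. With class ICC 0 it rejected in 4.9%. The Monte Carlo standard error is about 0.5 percentage points.

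**The averaged primary endpoint.** The article gives no within-person correlation, so 0.6 is assumed here. In units of the single-visit variance, a person's three-visit mean has variance (1 + 2 × 0.6)/3 = 0.733. If the class effect has relative weights w at 3, 6 and 12 months, its variance in the mean is 0.04 × (mean of w)². With 12 per class:

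| Class effect over time | Weights | ICC of the mean | DE | SE ratio | Actual error |
|---|---|---|---|---|---|
| Fully persistent | 1, 1, 1 | 0.04/0.733 = 0.055 | 1.60 | 1.140 | 8.6% |
| Fading (assumed) | 1, 0.5, 0.25 | 0.0136/0.733 = 0.019 | 1.20 | 1.050 | 6.2% |
| At 3 months only | 1, 0, 0 | 0.0044/0.733 = 0.006 | 1.07 | 1.017 | 5.4% |

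**Power of the averaged endpoint with clustering.** For the fully persistent case, SE = 0.20 × √(0.733 × (1 + 1.60)/234.4) = 0.0180, and power = Φ(0.06/0.0180 − 1.96) = 91%, before any gain from baseline adjustment. At correlations of 0.5, 0.7 and 0.8 it is 93%, 90% and 88%.

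**The case against.** The best defence is that the plan has not overlooked clustering. It quantifies the effect on power and commits to an analysis with class nested within arm, which is essentially the model a reviewer would ask for. The dispute is only over which of two planned analyses is primary. That is right and it limits the point, but the reported interval and p value still come from the model without class. Nor is this a detail left to the SAP: the article defers further covariates to it but states the random effects itself.

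The ICC of 0.04 is introduced conditionally, as a what-if for power. This stands too, so no single error rate can be asserted. Classes also run for only 12 weeks and start within 3 weeks of randomisation, so the 6- and 12-month visits fall well after they end. If class effects fade, the excess error is small. The inflation also requires real variation between classes together with a zero average effect; if class membership affects nobody, the test holds its level.

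Two stronger readings are tempting and are not supported. A reader might infer that the stated 90% power is wrong because clustering cuts it to 84%. The article discloses both figures, and says that the repeated-measures gain is not counted. With that gain the averaged endpoint has about 91% power even with a persistent class effect, under the assumed correlation of 0.6. A reader might also infer that nothing says which analysis prevails if the two disagree. The article presents the patient-and-site model as the analysis of the primary outcome and the class analyses as additional, so the order is clear. The difficulty is that the order favours the model with the smaller standard error.

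**Conclusion.** The point holds in conditional form. The primary model omits a source of variance that the sample size section recognises, and the site effect does not replace it, so the primary interval is too narrow whenever class variance is present. At ICC 0.04 and a single time point, the SE should be 8–10% larger and the test runs at about 7.0–7.6% (9.6 to 12 analysed per class). For the three-visit average with 12 per class, the error lies between about 5.4% and 8.6%, depending on how far class effects outlast the course and assuming a within-person correlation of 0.6. It returns to about 5% with no class variance. The inflation is modest, but it affects the trial's main test, and the primary model cannot credibly be changed once results are known.

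**What to change.** In {20a}, make the class-nested model the primary analysis: a class random effect in the intervention arm only, with small-sample degrees of freedom (Kenward-Roger or Satterthwaite) because there are only about 24 classes. Report the patient-and-site model as a sensitivity analysis.

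In {14}, label the 84% as the single-time-point power with clustering that corresponds to this model, before any gain from repeated measures or baseline adjustment. It should not be presented as the power of the repeated-measures primary analysis. The 90% figure can stand as the calculation without clustering.

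The change is one of wording in the protocol and SAP. Class attendance registers are already planned, so no new data are needed. The downside is a slightly wider interval: about 10% at the plan's ICC with 12 per class at a single time point, and less if class effects are weaker or fade.

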#### Interim analyses {21b}

There are no planned interim analyses for the trial or stopping guidelines. There is, however, an internal pilot study from which data will contribute to the final analyses. The primary reason for this pilot study will be to check the assumptions about recruitment and feasibility of the trial. The period covering the two waves of yoga courses at the four pilot sites will form the internal pilot phase. Descriptive statistics will be used to evaluate the four following progression criteria and inform study continuation beyond the pilot phase:
Intervention provision
Green: 3–4 sites offering their first group yoga session within 3 weeks after randomisationAmber: 1–2 sites offering their first group yoga session within 3 weeks after randomisationRed: 0 sites offering their first group yoga session within 3 weeks after randomisationIntervention acceptability
Green: ≥80% for overall class attendance rateAmber: 65–80% for overall class attendance rateRed: < 65% for overall class attendance rateRecruitment
Green: 3–4 sites recruited ≥20 patients each within 4 monthsAmber: 1–2 sites recruited ≥20 patients each within 4 monthsRed: 0 sites recruited ≥20 patients each within 4 monthsSix-month follow-up
Green: ≥80% completion of the EQ-5D-5LAmber: 65–80% completion of the EQ-5D-5LRed: < 65% completion of the EQ-5D-5L

If any criteria are graded as amber, a rescue plan will be developed outlining steps to be taken to improve intervention provision, recruitment, class attendance, and/or outcome follow-up (as appropriate) and will be agreed upon with the Trial Steering Committee and the funder. If all the progression criteria are failed (red), then the trial will not continue beyond the pilot phase.

### Methods for additional analyses (e.g. subgroup analyses) {20b}

#### Process evaluation analysis

Data analysis will be ongoing and iterative throughout the trial. Interviews will, with consent, be audio-recorded, transcribed verbatim, and edited to ensure respondent anonymity. Contemporaneous field notes from observations will also be edited to ensure participant anonymity. The analysis will be theoretically informed by the Normalisation Process Theory [37, 38] and will be conducted according to the standard procedures of rigorous qualitative analysis [39] including open and focused coding, constant comparison, memoing [40], deviant case analysis [41], and mapping [42]. Independent coding and cross-checking will be conducted, and a proportion of data will be analysed collectively in ‘data clinics’ where the process evaluation team share and exchange interpretations of key issues emerging from the data.

The process evaluation team will present anonymised emerging findings to the Trial Management Group on the potential determinants of trial set-up and recruitment. These might include site-specific issues, issues across multiple sites, or at the level of the organisation of the trial. Where necessary, the process evaluation team will work with the Trial Management Group and specific sites to develop and implement action plans. The focus will be on aspects of trial management and delivery that are amenable to change and all feedback will be supportive and constructive.

#### Cost-effectiveness analysis

The economic analysis will assess the relative cost-effectiveness of the GYY programme in addition to continued access to usual care compared with usual care alone. Costs and health outcomes will be evaluated from the perspective of the NHS and Personal Social Services, consistent with that used by NICE [43]. Data on healthcare resource use, intervention costs, and health outcomes will be collected during the 1-year trial period. Costs components will comprise primary and social care consultations (e.g. with a GP, nurse, or physiotherapist), hospital visits (e.g. inpatient episodes, outpatient visits, and accident and emergency admissions), and private treatments. Prescription data will also be obtained from GP practice records for up to 100 participants and covering the 15-month period before the 12-month follow-up. Trial records will be used to estimate the cost of the yoga intervention. Private expenditures related to treatment will also be recorded, and these costs will be included in a secondary analysis. We will estimate the cost per participant by multiplying the use of resource use by their associated unit cost, which will be valued using national published sources such as NHS reference costs and the British National Formulary. Health outcomes will be expressed in terms of the QALY using the EQ-5D data collected at baseline and 3, 6, and 12 months of follow-up. QALYs will be calculated by plotting the utility scores at each follow-up point and estimating the area under the curve [44]. Costs and QALY data will be synthesised to generate an incremental cost-effectiveness ratio (ICER), which is defined as the ratio of the mean difference in costs to the mean difference in QALYs between both arms of the trial. For the analysis, regression methods will be used to allow for differences in prognostic variables. The pattern of missing data will be analysed and handled by means of multiple imputations if deemed appropriate according to the missing data pattern in the dataset [45, 46]. Sensitivity analyses will be conducted to test the robustness of the results, including probabilistic sensitivity analysis. The uncertainty will be presented using a cost-effectiveness acceptability curve, which shows the probability of the yoga intervention plus usual care being more cost-effective than usual care alone. The probability that each intervention is cost-effective will be reported at the cost-effectiveness thresholds applied by NICE of £20,000 to £30,000/QALY [43] and also £13,000/QALY as suggested by recent research [47, 48]. A cost-consequence analysis will also be conducted to capture the wider consequences of the yoga intervention in terms of the full breadth of outcomes measured in the trial. A detailed health economics analysis plan will be agreed upon with the Trial Steering Committee before all data has been collected.
